### Multicomponent exercise program

Feasibility and safety of the multicomponent exercise program were ascertained in a previous study which included full details on volume, intensity, and type of strength and balance exercises [32, 33]. Participants allocated to this group will attend a twice-a-week multicomponent exercise program of one-hour duration per session, consisting of strength and balance exercises conducted by an experienced physical trainer. Participants will also continue attending their usual activities and workshops.

### Dual-task program

In the dual-task program, individually tailored cognitive tasks relying predominantly on executive function will be conducted concurrently with approximately four of the multicomponent exercises (Table 1).

**Table 1 Tab1:** Programation of the intervention for the 5th week

Objective	Sesion 1	Sesion 2
Warm-up 5 min	Range of motion for different joints	Range of motion for different joints
Strength training	–	Arm curl 60% 2 sets 8–12 rep + DAT (cog)
	Chair stand 60% 2 sets 8–12 rep	Chair stand 60% 2 sets 8–12 rep
	Leg flexion 60% 2 sets 8–12 rep + DAT (cog)	–
	–	Leg extension 60% 2 sets 8–12 rep + Inhibition task
	Leg abduction 60% 2 sets 8–12 rep + Calculus task	–
	–	Hip extensión 60% 2 sets 8–12 rep
	Standing on tips and heels 3 sets 10 rep + SAT	Standing on tips and heels 3 sets 10 rep + SAT
Balance training	–	Feet together stance 2 sets 10 s + DAT (physical)
	One legged stand 2 sets 10 s	–
	Semi-tandem/Tandem 2 sets 10 s + DAT (physical)	Semi-tandem/Tandem 2 sets 10 s + DAT (cog)
	Circuit training 2 sets	–
	–	Stepping 2 sets 10 rep
	Ball reaching 2 sets + Semantic memory	–
Cool down 5 min	Stretching, breathing, relaxing exercises.	Stretching, breathing, relaxing exercises.

*rep* repetitions, *DAT* divided attention task, *cog* cognitive, *SAT* sustained attention task

The challenge of dual-task-s will be increased by augmenting the complexity of motor tasks (progressing from sitting to standing and from static to dynamic exercises, reducing base of support, etc) (Table 2) and/or cognitive tasks (number of stimuli, complexity of word categories, etc.) (Table 3).

**Table 2 Tab2:** Detailed description of the general DT group intervention

3 MONTHS			
Objective	1ST MONTH Familiarisation phase	2ND MONTH Strength development Static balance DT	3RD MONTH Strength maintenance Dynamic balance DT
Strength	3–4 ex: 1–2 sets, 8–12 rep at 40–50% of 1RM	4–5 ex: 2 sets, 8–12 rep at 60% of 1RM	4–5 ex:1–2 sets, 8–12 rep at 65–70% of 1RM
Balance	2–3 ex, progressive difficulty in sitting position and progressing to standing position.	4–5 ex, progressive difficulty in standing position with decreasing arm support and increasing instability.	
Dual-task	In 3–4 of strength ex	In 2–3 of strength ex and 1–2 of balance ex	In 1–2 of strength ex and 3–4 of balance ex

*ex* exercises, *rep* repetitions

**Table 3 Tab3:** Progression of complexity of secondary tasks by levels of difficulty

Main cognitive function		Level 1	Level 2	Level 3	Level 4	Level 5
Attention	Divided (cognitive) *CATEGORIES:Buildings/ Dairy products/ colors*	The participant will repeat a specific word from a certain category (e.g house) every time the instructor says *it*	The participant will raise a hand every time the instructor says a specific word from a certain category or when a green card is presented	The participant will raise a hand every time the instructor says two specific words from certain categories or when a green card is presented	The participant will raise a hand every time the instructor says two specific words from certain categories or when a green card is presented or when the instructor claps	The participant will raise a hand and repeat the word every time the instructor says two specific words from certain categories or when a green card is presented or when the instructor claps
	Divided (physical)	Participants will carry out the physical task whilst maintaining a cup with a ball upright to avoid the ball from falling				
	Sustained	Naming months of the year forward	Naming months of the year forward starting from a random month	Naming even or odd months of the year forward	Naming months of the year backwards	Naming months of the year backwards starting from a random month
	Shifting	Participants will be asked to shift focus from a cognitive task to another on some of the dual tasks				
Semantic fluency		Naming colors/days of the week/names	Naming members of the family/clothes	Naming professions	Naming cooking instruments or general tools	Naming fish, dog or tree types
Inhibition		If the instructor says *YES* they respond *NO* and viceversa	Every time the instructor says HEADS they have to answer TAILS and viceversa and Previous entry	If a green card is presented they have to say RED and when a red card is presented they have to say GREEN	Level 2 and level 3 instructions altogether	If the word RED is presented in a green color they have to say *GREEN* and vice versa and when the word YES in red color or NO in green color, they have to name the colo*r*.
Problem solving (calculus)		Counting by twos starting from a number ≥ 30	Counting by threes from a number ≥ 50	Substracting by twos from a number ≥ 30	Substracting by threes from a number ≥ 50	Substracting by fours from a number ≥ 100
Movement coordination		Inherent to the muticomponent exercise program				
Movement learning and sequencing						

The first week of the intervention will mainly serve to familiarize participants with the strength and balance exercises and adjust the level of difficulty of each cognitive function task to every participant in the group. In the second week, strength tests will be performed to individualize strength training and ensure training intensity. Throughout the following weeks, dual tasking will be applied mostly in strength exercises to train for divided attention allocation and will progressively move to balance exercises to optimize training adaptations and mimic everyday situations that require double tasking and increasing instability.

Cognitive training will be conducted based on six main cognitive functions essential for everyday life activities (Table 3). One of the most important functions to train is attention, which will be applied in form of: 1) divided attention tasks (with a secondary physical or cognitive task) where participants will have to divide their attention to ensure task achievement; 2) sustained attention tasks, in which attention will have to be maintained throughout a certain time period (1–2 min); 3) shifting, where participants will have to shift their focus of attention between cognitive tasks. In addition, semantic fluency will consist of naming words according to different categories with increasing difficulty such as naming animals, professions or even dog breeds. Other executive functions including calculus or inhibitory control will also be trained, the latter consisting of overriding the natural response to certain stimuli. Finally, due to the fact that movement coordination, movement learning and sequencing are inherent to any exercise-based program, these will be present in both the multicomponent exercise program group and in dual-task group.

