### Inclusion and exclusion criteria, recruitment, and randomization

The inclusion criteria, recruitment, and randomization methodologies in the Aging-ON_DUAL-TASK_ study will be the same as on a previously published protocol [33]. The inclusion criteria will be: age ≥ 70 years old; a Barthel Index [34] score ≥ 50 and score ≥ 20 on the MEC-35 Test [35] [Mini-examen cognoscitivo, an adapted and validated version of Mini Mental State Examination (MMSE) in Spanish]; and capacity to stand up and walk independently for at least 10 m. Participants will not be eligible if they are judged clinically unstable by the medical staff, or have in any other condition in which entering the study would not be in the subject’s best interests.

Identification of individuals that meet the inclusion criteria will be facilitated by the databases of the included long-term nursing homes. The primary recruitment strategy will be information provided to the potential participants by the medical and nursing professionals from each facility. All volunteers will receive detailed study information at their reference sites through the research team: objectives, measurement variables, and other details about the interventions will be explained orally and in writing to both potential participants and their families. After signing the informed consent, the participants within each center will randomly be assigned (in a 1:1 ratio) through sealed opaque envelopes to either the multicomponent or the dual-task group by coin-tossing sequence generation.

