### Power and sample size

Sample size for the current study was calculated to detect a significant clinical difference on the dual-task gait speed test [54]. Accepting an alpha risk of 0.05 and a beta risk of 0.20 in a bilateral contrast, 141 individuals are required to detect a difference equal to or greater than 0.08 m/seg in the dual-task gait speed test (SD = 0.24). The sample size was increased by 20% to account for losses during follow-up and an additional 5% for mortality. The resulting sample size is 188 individuals, allocating 94 participants to each group.

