### Statistical considerations

Data analysis will be performed using the IBM SPSS Statistics 24 statistical software package (SPSS, Inc., Chicago, IL). Intention-to-treat analyses will be performed and the level of statistical significance will be set at *p* < .05 for all computations. First, all data will be checked for normality of distribution using the Kolmogorov-Smirnov test. Results will be expressed as mean (with standard deviation) for continuous and normally distributed variables and as median (with interquartile range) when normality of data for that variable cannot be assumed. In the case of categorical variables, frequency counts and percentages will be used to describe the results. Tests for baseline comparisons will be selected based on the nature and distribution of the data: Student’s-t test with continuous and normally distributed variables, Mann-Whitney test with non-normally distributed continuous variables, and Chi-squared test with categorical variables.

To test the effects of training interventions, mixed-designed ANCOVA-s or the Friedman test, including baseline measurements, age, or gender as covariates, will be performed for physical, cognitive, and emotional variables. In cases where a significant F value is found, LSD post hoc procedures will be performed for pairwise comparisons.

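### If training sessions are shared within home and arm, as the text suggests, neither the sample size nor the ANCOVA allows for the resulting correlation, and the ANCOVA also omits home

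*Protocol article*

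**What the plan says.** **Randomisation** (Inclusion and exclusion criteria, recruitment, and randomization): "the participants within each center will randomly be assigned (in a 1:1 ratio"), by coin toss and sealed envelopes. Study design and participants gives eight homes with at least 16 residents each.

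**Delivery.** The multicomponent programme consists of two one-hour sessions a week, "conducted by an experienced physical trainer". In the Dual-task program section, Table 1 sets out one session plan for week 5, and Table 3 has an instructor who calls words, claps or shows cards. The text after Table 3 says that week one serves to "adjust the level of difficulty of each cognitive function task to every participant in the group". Session size, number of trainers and whether sessions are shared are not given.

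**Sample size** (Power and sample size): for a two-sided alpha of 0.05 and power of 0.80, the article states that "141 individuals are required to detect a difference equal to or greater than 0.08 m/seg", taking the SD as 0.24. This is inflated to 188 for losses and mortality only.

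**Analysis** (Statistical considerations): "mixed-designed ANCOVA-s or the Friedman test, including baseline measurements, age, or gender as covariates, will be performed". Home, trainer and session group do not appear.

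**The concern.** Residents who train together share an instructor, a pace and a social setting, so their 3-month gait speeds may be correlated. If each arm in each home has its own sessions, that correlation sits at the home-by-arm level. It does not cancel between arms and enters the treatment contrast directly. A main effect for home cannot remove it.

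Home itself behaves differently. Residents of both arms live in the same home, so a home effect is largely shared by the two arms. Leaving it out tends to waste precision, not to create false positives. The plan therefore has two gaps that act in opposite directions, and the net effect on the primary p-value cannot be read off the plan. At stake is whether the confidence interval for the dual-task gait speed difference has its stated coverage.

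**Working it through.** **1. The plan's own figure.** The inputs, from Power and sample size, are difference 0.08 m/s, SD 0.24, two-sided alpha 0.05 and power 0.80.

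n per arm = 2 × [0.24 × (1.960 + 0.842) / 0.08]² = 141.3, which rounds up to 142 per arm, or 284 in total.

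The stated 141 is therefore the per-arm number, but it is used as the total: 141 / (1 − 0.25) = 188, split 94 and 94. The formula treats residents as independent, with no design effect. With 141 evaluable in total, SE = 0.24 × √(4/141) = 0.0404. Power = Φ(0.08/0.0404 − 1.96) = 51% before any clustering. Baseline adjustment could recover this, but 142 in total would need a baseline correlation of about 0.71, which is not stated.

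**2. Assumed group structure.** One session group per arm and home gives 8 × 2 = 16 groups. Group size is then 141/16 = 8.8 completers, or 188/16 = 11.75 if all are analysed. The ICC (ρ) is also assumed. It refers to the scale analysed, that is, after baseline adjustment where that is done.

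**3. Simple design effect.** DE = 1 + (m − 1)ρ. The true type I error of a test that ignores the grouping is 2 × [1 − Φ(1.96/√DE)]. Power is for a test with the correct standard error: the normal approximation of step 1 with the SE multiplied by √DE, 141 evaluable, no baseline gain and no small-sample penalty.

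| ρ | DE (m = 8.8) | Type I | Power | DE (m = 11.75) | Type I |
|---|---|---|---|---|---|
| 0 | 1.00 | 5.0% | 51% | 1.00 | 5.0% |
| 0.01 | 1.08 | 5.9% | 48% | 1.11 | 6.3% |
| 0.02 | 1.16 | 6.8% | 45% | 1.21 | 7.5% |
| 0.05 | 1.39 | 9.7% | 39% | 1.54 | 11.4% |

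**4. Home in the model, session group ignored.** Take 8 homes, 2 arms and m = 9. The residual has 144 − 9 = 135 degrees of freedom, 7 of them home-by-arm. The variance that drives the contrast is 1 + 8ρ. The variance that the model estimates is on average (1 − ρ) + 9ρ × 7/135.

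- ρ = 0.01: 1.08/0.995 = 1.086, type I error 6.0%
- ρ = 0.02: 1.16/0.989 = 1.173, type I error 7.0%
- ρ = 0.05: 1.40/0.973 = 1.438, type I error 10.2%

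**5. Home left out, as the article's covariate list reads.** This was simulated with a plain t-test, 9 per group and arms balanced within homes, 20,000 runs per setting.

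| Home ICC | Session-group ICC | Rejections under the null |
|---|---|---|
| 0.05 | 0 | 4.6% |
| 0.10 | 0 | 3.9% |
| 0.10 | 0.01 | 4.9% |
| 0.10 | 0.05 | 9.1% |

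A strong home effect can thus hide a small session-group effect but not a moderate one. The offset relies on the arms being balanced within homes, which coin tossing does not guarantee.

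**The case against.** The strongest objection is that shared delivery is inferred. The article often uses the word group to mean the arm, and the key phrase can be read that way. Cognitive tasks are tailored to the individual and strength loads are individualised. Full exercise details are referred to an earlier protocol that is not shown. This stands, and it is why the point is conditional. The single session plan and the instructor cues make shared sessions the likelier reading, not a documented fact.

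Second, the size depends on unknowns. At an ICC of 0 to 0.01 the error is 5% to about 6%. If each arm in each home were split into two sessions (m about 4.4), an ICC of 0.05 gives DE 1.17 and about 7%. An ICC of 0.10 would imply a between-group SD of √0.10 × 0.24 = 0.076 m/s on the raw scale, nearly the whole 0.08 m/s target. No weight is placed on so high a value here. All of this stands.

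Third, a reader might infer that a trainer effect could pass for a dual-task effect. The document does not say how many trainers there are or whether they differ by arm. If one trainer leads both arms in a home, that trainer's common effect cancels.

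Fourth, a separate analysis plan could add the missing terms. That is possible. But the sample size is complete as printed, and the covariates for the effect analysis are named without home or session group.

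**Conclusion.** The point holds conditionally. If sessions are shared within home and arm and the session-group ICC is above zero, neither the sample size nor the ANCOVA as named allows for it. With home in the model, the type I error is then about 6% to 10% for ICCs of 0.01 to 0.05. This rests on two assumptions: 16 groups of about 9 completers, and that ICC range.

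A reader might conclude that the trial's actual type I error exceeds 5%. The document does not support this: it states neither shared sessions nor an ICC, and omitting home can offset a small group effect. Nor does clustering by home as such inflate the error.

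A reader might also express the loss as a reduced effective size out of 141. That would start from the wrong base, because the stated inputs need about 142 per arm.

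The omission of home needs no such condition: it is the level within which residents are randomised and belongs in the model. The matter should be settled before the analysis, since session membership is hard to reconstruct later.

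**What to change.** 1. State how sessions are delivered, and record each resident's session group and trainer.
2. Fit 3-month dual-task gait speed on arm, baseline value and home. Where sessions are shared, add a random effect for session group (home by arm). Use small-sample degrees of freedom such as Satterthwaite.
3. Report the estimated session-group ICC with the primary result.
4. Correct the base of the sample size statement first (about 142 per arm from the stated inputs). Then restate the power of the planned 188 over a range of ICCs, with the assumed group size and any assumed baseline correlation. Enrolment need not be raised for this point.

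**Cost.** This needs two recorded variables and a change of analysis wording. The interval will be wider. With 8 homes the arm contrast may have as few as about 8 − 1 = 7 degrees of freedom, where the critical t is about 2.36 instead of 1.96. With 16 groups the variance component will be imprecise, and the stated power will look less favourable.

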### Outcome measures

The primary outcome measure will be gait speed under dual-task conditions. The distance to be covered will be 9 m on a smooth non-slippery surface with starting and ending points marked on the floor with tape. The cognitive task to be performed will previously be explained to participants. Straight after the explanation, the participant will be asked to walk at a comfortable pace on a straight line while simultaneously performing the cognitive task. Time to perform the test will be measured following the procedure described by Bohannon [36]. Gait speed will be then calculated dividing the covered distance (in meters) by the employed time (in seconds).

In addition, both gait spatiotemporal parameters (cadence, single and double support time, etc.) and cognition (number of correct, incorrect and total responses) will be analyzed, and compared with performance in the single-task modality. This difference is referred to as dual-task cost, and will be calculated using the formula: ((dual task – single-task)/single-task × 100) [18].

Secondary outcome measures will include functional (Table 4), cognitive, and emotional assessments (Table 5). Functional capacity will be determined by the following tests (Table 4): the Short Physical Performance Battery test [37] (SPPB); the Senior Fitness Test [38] (SFT); the instrumented Timed Up and Go test [39] (iTUG; BTS Biomedical G-WALK triaxial accelerometer and gyroscope); usual walking speed [36]; the handgrip strength test [40] (Jamar dynamometer) and Berg balance test [41]. Frailty assessment will include the Tilburg Frailty index [42], the Frailty index [43] and the Rockwood clinical frailty scale [44]. In addition, participants will wear an accelerometer (Actigraph GT3X model (Actigraph LLC, Pensacola, FL, USA)) on the hip with a belt for 7 days to measure active and sedentary periods during everyday life, by daily step quantification. Active-period intensities will be classified as light, moderate or vigorous based on Freedson and colleagues’ criteria [45] and recorded in minutes.

**Table 4 Tab4:** Functional assessment tests

Test (Reference)	Functions/Parameters	Description
Short Physical Performance Battery (SPPB) (Guralnik et al., 1994)^a^	Lower extremity function: static balance, gait speed and getting in and out of a chair	Side-by-side, semi-tandem and tandem stands (10 s); 4 m walk test at comfortable speed and 5 quickly sit to stand from a chair without upper extremity assistance
Senior Fitness Test (Rikli & Jones, 2007)^a^	Upper and lower extremity strength and flexibility, static and dynamic balance and aerobic capacity	Chair-stands in 30 s; 6-min walking test; arm curl test (30 s); chair sit and reach; back scratch and 8 Foot Up and Go test
Instrumented Timed Up and Go test (BTS Biomedical G-WALK) (Mathias et al., 1986)^a^	Dynamic balance	Get up from a chair, walk 3 m at a normal pace, turn and walk back to sit down again
Instrumented walking speed (BTS Biomedical G-WALK) (Bohannon et al., 1996)^a^	Standard gait parameters: speed, step frequency, cadence	Walk for 4 and 9 m at comfortable speed
Bilateral handgrip strength test (Jamar dynamometer) (Fess, 1992)^a^	Hand grip strength	Squeeze the dynamometer with maximum isometric effort for about 5s
Berg balance test (Berg et al., 1992)^a^	Postural stability	Performance of 14 functional tasks
Accelerometry [Actigraph GT3X model (Actigraph LLC, Pensacola, FL, USA)] (Freedson et al., 1988)^a^	Active and sedentary periods during everyday life	7 days period quantification of the number of steps performed per day and minutes completed at light, moderate or vigorous intensity

^a^Rodriguez-Larrad et al. [33]

**Table 5 Tab5:** Cognitive and Emotional assessment tests

Test (Reference)	Functions	Description
Montreal Cognitive Assessment (MoCA) (Coen et al., 2016)^a^	Mild Cognitive Impairment, Early Alzheimer’s disease	Covered domains: attention and concentration, executive functions, memory, language, visuoconstructional skills, conceptual thinking, calculations, orientation
Wechsler Adult Intelligence Scale (WAIS-IV) (Wechsler et al., 2010)	Cognitive impairment	Covered domains: attention, visual scanning, motor speed
Trail Making Test (TMT) (Reitan, 1958)	Cognitive impairment	Assesses: visual-conceptual and visual-motor tracking, sustained attention and task alternation abilities
Rey Auditory Verbal Learning Test (RAVLT) (Lezak, 1995)	Memory and learning capacity	Evaluates short- and long-term verbal memory assessing the ability to learn a list of 15 common words
Anxiety and Depression Goldberg Scale (Goldberg et al., 1988)^a^	Affective state	Includes nine depression and nine anxiety items from the past month
The Jong Gierveld loneliness scale (de Jong-Gierveld, 1987)	Emotional and social loneliness	Includes characteristics of the social network, background variables, personality characteristics, and evaluative aspects
Questionnaire QoL-AD (Logsdon et al., 2002)	Perceived quality of life	Self-rated quality of life for people with cognitive impairments

^a^Rodriguez-Larrad et al. [33]

For cognitive and emotional assessment (Table 5), participants will be assessed through the Montreal Cognitive Assessment [46] (MoCA), the Coding and Symbol Search test (which provide a measure of processing speed) from the Wechsler Adult Intelligence Scale, Fourth Edition (WAIS-IV) [47], the Trail Making Test part A [48] (TMT), the Rey Auditory Verbal Learning Test [49] (RAVLT), the Anxiety and Depression Goldberg Scale [50], the Jong Gierveld loneliness scale [51], and the Quality of Life Alzheimer’s disease scale [52] (QoL-AD).

The following additional variables will also be registered: sociodemographic variables: age, gender, socioeconomic situation, educational level, and marital status; level of independence in activities of daily living: Barthel index [34]; cognitive impairment assessed through MEC-35 [35]; anthropometric measurements: weight, height, body mass index, waist and hip circumferences, and waist-to-hip ratio; and clinical outcomes Charlson comorbidity index [53], number of falls, visits to the emergency service, number and length of hospitalizations, death rates, and medication.

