In consonance with this idea, an impaired capacity to perform attention-demanding mobility activities such as carrying out two tasks (physical + cognitive) simultaneously, also known as *dual-task*, could be a novel marker of physical and cognitive frailty. Many activities of daily life involve the performance of several tasks at a time, creating competing demands for attentional resources that challenge both motor and cognitive functions [14]. Considering that attentional capacity is limited, when demands exceed capacity, performance of dual-tasks can be affected compared to performance of the same tasks in a *single-task* fashion. Indeed, older adults show greater impairments compared to their younger counterparts in cognitive-motor dual-task performance, such as naming animals while walking or making calculations during balance exercises [15, 16]. Additionally, low dual-task performance capacity is associated with cognitive impairment and with a high risk of falling [17–19].

Previous studies of dual-task as a test of functional performance in older adults have focused on the gait speed test or on the Timed Up and Go test as physical tasks, while introducing semantic fluency or a calculus command as cognitive content. The difference between performance in the dual-task and the single-task tests is known as *dual-task interference* or *dual-task cost* [20]; this difference increases with aging [21]. The dual-task cost can be accounted for in both the physical and the cognitive domains. In this regard, the most commonly used formula is: dual-task cost = ((dual task − single task) single-task) × 100% [18]. For the physical dual-task cost calculation, time in seconds is used, whereas for the cognitive dual-task cost, either the number of correct responses or the percent of correct responses can be used to compare between single and dual task performances.

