### Dual-task assessment

The secondary tasks included in the dual-task evaluation will be of three different natures: 1) semantic fluency: naming animals or fruits and vegetables; 2) backward counting by ones; and 3) inhibition ability through the Go no go test (when the evaluator says ‘one’, the participant has to respond ‘two’ and viceversa). We selected these tasks by the following process: a) a review of the literature, b) expert consultation through interviews and a discussion group, c) final selection.

Cognitive tasks will be applied during two different physical function tests: 9 m usual gait speed and the Timed Up and Go test. In addition, these physical tasks will be performed in a single task mode to allow for dual-task cost calculation. Dual-task gait speed and dual-task Timed Up and Go tests will be performed on two non-consecutive testing days to minimize learning effects and the order of the dual-task and the single-task will be randomized for the same purpose. In addition, participants will wear an accelerometer (BTS Biomedical G-WALK triaxial accelerometer and gyroscope) during the tests to measure gait kinematic parameters such as step number, cadence, step symmetry, and step time variability. The number of total responses, errors, repetitions, and stops will be recorded. No instructions will be given regarding task prioritization.

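### Dual-task response counts over a fixed 9 m walk depend on walking time, so a gain in gait speed by itself lowers correct, incorrect and total counts

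*Protocol article*

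**What the plan says.** The primary outcome is dual-task gait speed. Under Outcome measures, the course is fixed: "The distance to be covered will be 9 m on a smooth non-slippery surface". Participants "walk at a comfortable pace on a straight line while simultaneously performing the cognitive task", and time is measured: "Gait speed will be then calculated dividing the covered distance (in meters) by the employed time (in seconds").

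The same section then adds the response measures: "cognition (number of correct, incorrect and total responses) will be analyzed, and compared with performance in the single-task modality". The comparison is made through dual-task cost, with the formula "dual task – single-task)/single-task × 100".

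Under Dual-task assessment, the items collected are again counts: "The number of total responses, errors, repetitions, and stops will be recorded". Three kinds of task are used: semantic fluency, backward counting, and an inhibition task in which the participant answers the evaluator's prompts. They are applied during the 9 m walk and during the Timed Up and Go, which Table 4 describes as 3 m out and back, so also a fixed course. On the single-task side, the section says that "these physical tasks will be performed in a single task mode to allow for dual-task cost calculation".

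The Introduction notes that for cognitive dual-task cost "either the number of correct responses or the percent of correct responses can be used". The Methods name numbers of responses and do not mention a percentage. No section divides responses by time.

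**The concern.** A count collected over a fixed distance is a response rate multiplied by a walking time, and the intervention is meant to shorten that walking time. If the dual-task arm walks faster, as hypothesised, its participants have less time to respond. Their counts then differ from those of the other arm even when both arms respond equally fast and equally accurately.

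The distortion runs in two directions. Fewer correct and total responses look like worse cognition, while fewer errors look like better cognition. Adjusting for baseline value, age or gender, as the Statistical considerations section proposes, does not remove this, because the distortion comes from walking time at follow-up.

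The stake is interpretation. The Discussion says the trial examines both gait and cognitive aspects of dual-task performance, and participants get no instruction on which task to prioritise. A reader will naturally look at the responses to see whether faster walking came with neglect of the cognitive task. Raw counts do not answer that cleanly.

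**Working it through.** There is no figure in the plan to reproduce here; the check is algebraic.

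**Inputs from the article**
- Distance 9 m, fixed (Outcome measures).
- Hypothesised gain d = 0.08 m/s (Introduction; Power and sample size).
- Cost = (dual − single)/single × 100 (Outcome measures).

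**Assumptions**
- Baseline dual-task speed v of 0.40, 0.60 or 0.80 m/s, because the article gives none.
- A response rate r that is constant during the walk.

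**Step 1: effect of speed on the count.** Expected count = r × 9/v. If speed rises to v + d and r does not change, the relative change is v/(v + d) − 1 = −d/(v + d). The rate cancels, so the result holds for correct, incorrect and total responses alike. It also describes the contrast between two arms whose speeds are v and v + d.

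**Step 2: break-even.** The correct count stays level only if the rate of correct responses rises by a factor (v + d)/v, that is by d/v.

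| Assumed v (m/s) | Time before (s) | Time after (s) | Change in count, −d/(v + d) | Rate rise needed to break even, d/v |
|---|---|---|---|---|
| 0.40 | 9/0.40 = 22.50 | 9/0.48 = 18.75 | −16.7% | 20.0% |
| 0.60 | 9/0.60 = 15.00 | 9/0.68 = 13.24 | −11.8% | 13.3% |
| 0.80 | 9/0.80 = 11.25 | 9/0.88 = 10.23 | −9.1% | 10.0% |

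**Step 3: effect on cognitive dual-task cost.** This is an illustration with assumed values: v = 0.60 m/s, 0.8 correct responses per second while walking, and a single-task reference of 1.0 per second over a fixed 15 s (15 responses).

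| Situation | Correct count | Count-based cost | Rate-based cost |
|---|---|---|---|
| 0.60 m/s, 0.80/s | 0.80 × 15.00 = 12.0 | (12.0 − 15)/15 = −20.0% | (0.80 − 1)/1 = −20.0% |
| 0.68 m/s, 0.80/s | 0.80 × 13.24 = 10.59 | (10.59 − 15)/15 = −29.4% | −20.0% |
| 0.68 m/s, 0.88/s | 0.88 × 13.24 = 11.65 | (11.65 − 15)/15 = −22.4% | (0.88 − 1)/1 = −12.0% |

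In the second row nothing cognitive has changed, yet the count-based cost worsens by 9.4 percentage points. In the third row the response rate has truly improved by 10%. That is below the 13.3% break-even, so the count-based cost still worsens while the rate-based cost improves.

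**Step 4: percent correct.** Add an assumed 0.1 errors per second. Before: 12.0/(12.0 + 1.5) = 88.9%. After: 10.59/(10.59 + 1.32) = 88.9%. Errors fall from 1.5 to 1.32 (−11.8%) without any gain in accuracy, and percent correct does not move.

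**The case against.** - **The article does not rule out other scores.** Correct, incorrect and total counts together give percent correct, the Introduction allows it for the cost, and test time is recorded. A full protocol or analysis plan could derive duration-free measures. This is fair, and it is why the remedy is easy. But the Methods do name the measure to be analysed, and they name numbers of responses. The point concerns that stated choice, not a missing detail.
- **The single-task cognitive reference.** A reader might infer that it is missing or defective, since only the physical tasks are described as performed alone. The article does not support that. It presupposes a single-task cognitive comparison, and the length of that test is a detail that an article may leave to the full protocol. If its duration were matched to the walk, part of the distortion in the cost would cancel; the raw counts would still depend on walking time.
- **Constant ability is not the expected case.** The dual-task arm trains fluency, calculation and inhibition, so its response rate may rise. This stands: above the break-even rise, correct counts would still show a gain, though a reduced one.
- **A rate is not perfect.** In the inhibition task a rate would partly measure the evaluator's pace. If fluency output slows as the walk proceeds, counts fall by less than the percentages above, and a rate would itself somewhat favour the faster walker. Both points stand, so the measure should differ by task and a rate should be read together with percent correct.

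**Conclusion.** The concern holds for the supplementary dual-task response measures. As written, these counts and the cost built on them depend on walking time. At an unchanged response rate, the hypothesised 0.08 m/s lowers expected counts by about 17%, 12% or 9% at assumed baselines of 0.40, 0.60 or 0.80 m/s. These percentages rest on the assumed speeds and on a response rate that is constant during the walk. For the Timed Up and Go the mechanism is the same, but its size cannot be given because the article states no expected gain.

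A reader might infer that any gait benefit must show up as cognitive decline, or that the trial will report a trade-off that does not exist. That goes too far. Apparent worsening of correct counts needs a rate rise below 0.08/v, and error counts are biased the other way, in favour of the faster arm. Nor does the point extend to cognition as a whole: MoCA, the WAIS-IV subtests, the Trail Making Test and RAVLT are separate from the walk, and the primary outcome is untouched. The change is worth making before analysis, but it does not threaten the main result.

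**What to change.** State the following for the 9 m walk and the Timed Up and Go:

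- **Semantic fluency and backward counting (self-paced):** analyse correct responses per second of recorded test time, together with percent correct.
- **Inhibition task (evaluator-paced):** analyse percent correct.
- **Cognitive dual-task cost:** compute it on these measures, with the single-task cognitive reference expressed on the same scale.
- **Raw counts:** report descriptively only.

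The cost is a small amount of extra derivation from counts and times that are already recorded.
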